**Other exploratory endpoints**
The difference in MAGE between the two diet periods^1^
The difference in HbA1c between the two diet periods
The difference in apolipoproteins between the two diet periods
**Safety endpoints**
The difference in the proportion of time with low blood glucose levels between the two diet periods (below 3.0 mmol/l and below 3.9 mmol/l respectively)^1^
The difference in the mean number of severe hypoglycemic events between the two diet periods defined as unconsciousness due to hypoglycemia or requiring assistance from another person
The difference in ketone levels between the two diet periods
Occurrence of ketoacidosis during the study period and differences between the two diet periods

^1^Measured with continuous glucose monitoring during the last 2 weeks of interventions.

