Few studies have examined the effects of lower carbohydrate diets in patients with T1D and results are conflicting. A systematic review (21) examined the effects of LCDs (<45% of total energy) on glycemic control in eight studies of adults and children with type 1 diabetes. The studies were heterogenic and of small size and the results conflicting. In a large European observational study, they could see a trend that a lower intake of total carbohydrates was associated with lower HbA1c (22). This was also reported in another observational study in Denmark where higher intake of carbohydrates was associated with higher HbA1c in persons with T1D (23). A Finnish observational study reported that adherence to LCD was associated with lower BMI, lower variability of blood glucose measurements and lower diastolic blood pressure (24). A small study (*n* = 11) showed that a ketogenic diet (carbohydrate <55 g/day) was associated with excellent HbA1c levels [35 ± 4 mmol/mol (5.3 ± 0.4%)] and little glycemic variability, although it was also associated with dyslipidemia and a high number of hypoglycemic episodes (25). The studies that have shown beneficial effects on glycemic control with LCD are small (26–29) and/or not randomized and lacking control groups (29, 30).

The aim of this study is to analyze the effects of a moderate carbohydrate diet (30 percent of total energy) compared with a traditional diabetes diet (50 percent of total energy) on glycemic control and risk of ketoacidosis in patients with T1D.

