### Design and randomization

2.1.

This is a randomized, open-label, cross-over clinical trial being conducted at four Swedish diabetes specialty centers. Enrolment commenced in March 2018 and study completion is expected during winter 2022. Patients were randomized 1:1 to either moderate carbohydrate or traditional diabetes diet for 4 weeks with an intermittent wash-out period of 4 weeks followed by the other intervention diet for 4 weeks. Expected study duration for each participant was 14–16 weeks, including a run-in period of 2–4 weeks. Eligible participants were identified from each diabetes center registry, and patients were invited to participate by written correspondence or telephone. Randomization was performed on site using a centralized web system with random permuted blocks of varying sizes. Each patient was assigned a unique coded subject ID at randomization.

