### Continuous glucose monitoring

2.4.

All patients used a masked continuous glucose monitoring (CGM) system (Freestyle Libre Pro, Abbott Diabetes Care) during a run-in period of 2–4 weeks and then continuously for the rest of the study period for a total of 14–16 weeks. Data were collected from the CGM system at all clinical visits. Patients using CGM or Intermittent scanned Continuous Glucose Monitoring (isCGM) in their usual diabetes care continued to use this as well. Missing data from the masked CGM sensor could be replaced by data from patients regular, non-blinded CGM/isCGM device in the statistical analyses if available. All deviations such as which devices were used were carefully documented.

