### Insulin adjustments

2.5.

Insulin adjustments were reviewed by a diabetes nurse or physician at the beginning of each treatment phase to ensure that participants adjusted insulin doses properly when changing diet. Clinical support was only provided at the start of each treatment phase, whereas during the evaluation period (last 14 days of each diet period) patients fully adjusted their doses on their own. Basal insulin and basal insulin dose in the insulin pump were adjusted by an algorithm primarily based on fasting blood glucose levels and overnight glucose profiles. At high fasting blood glucose levels and no tendency for nocturnal hypoglycemia the basal dose was increased in a stepwise fashion. Doses were reduced at low fasting blood glucose levels or nocturnal hypoglycemia. Glucose excursions at bedtime were also taken into consideration. For detailed algorithms see Supplementary material 1.

Patients were instructed to continue with the same strategy for dosing mealtime insulin as used in clinical practice (e.g., carbohydrate counting was continued if used). A dietitian educated patients about types of foods containing carbohydrates and provided similar support for both types of diets. A diabetes nurse or physician provided feedback at planned telephone contacts from glucose curves if apparent that mealtime doses were under- or overdosed to be taken into consideration for future mealtime insulin dosing. Patients were instructed to strive for 2-h post-meal glucose levels <10 mmol/l and pre-meal levels <7 mmol/l. Repeated glucose levels over these levels indicated that higher mealtime insulin doses were needed for that specific meal.

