The study period of 12 weeks and active intervention periods of each 4 weeks was planned to be relatively short since we wanted participants to comply to changes in diets and advanced study related procedures including food diaries, ketone levels and masked CGM. The main goal of the trial is to evaluate if different carbohydrate content in diet influences glucose levels. Moreover, the use of masked CGM-data for key endpoints capturing differences in glucose patterns continuously gives an opportunity to capture the current glucose effects during each treatment period. Hence, the current study will show if a lower content of carbohydrates in diet *per se* leads to more stable glucose levels and if ketone levels are influenced. However, it is important to notice that if the intervention diet leads to improved glucose control it will be essential to evaluate whether such a diet can be kept over long time periods with sustained effects on glucose control.

In summary, this study seeks to increase knowledge about the effects of dietary carbohydrate intake on glycemic control and other health parameters in patients with T1D. If beneficial effects on mean blood glucose level without elevated risk of hypoglycemia or ketoacidosis are shown, a moderate carbohydrate diet may be a treatment option for people with T1D that have unsatisfactory blood glucose levels. If shown to have no beneficial effects, this study will hopefully increase knowledge among healthcare professionals whether moderately decreasing carbohydrate intake is safe when educating patients about diet.

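### The CGM time-below-range safety endpoint covers only the last 14 of 28 days on each diet and omits the fortnight of diet change and supported insulin adjustment

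*Protocol article*

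**What the plan says.** Section 2.11, Table 3 of the protocol article lists four safety endpoints. The first is "The difference in the proportion of time with low blood glucose levels between the two diet periods (below 3.0 mmol/l and below 3.9 mmol/l respectively"), and it carries footnote 1: "Measured with continuous glucose monitoring during the last 2 weeks of interventions". The same footnote governs the primary endpoint and the other CGM endpoints. The other three safety endpoints (severe hypoglycaemic events, ketone levels, ketoacidosis) do not carry it.

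On timing, section 2.1 states: "Patients were randomized 1:1 to either moderate carbohydrate or traditional diabetes diet for 4 weeks with an intermittent wash-out period of 4 weeks". Section 2.5 states: "Insulin adjustments were reviewed by a diabetes nurse or physician at the beginning of each treatment phase". Section 2.10 puts the telephone contacts at days 1, 4, 7 and 14. Sections 2.5 and 2.11 define the last 14 days as the evaluation period, in which patients manage their doses without clinical support.

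On data, section 2.4 has masked CGM worn during run-in and then "continuously for the rest of the study period". The Abstract says that CGM was used throughout to evaluate hypoglycaemia, among other outcomes. Section 2.8 says that time in low glucose was recorded by CGM and gives no window. Section 3 counts it as a strength that continuous CGM gives detailed information on glucose fluctuations while the diet is being changed.

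On use, the Abstract and section 3 make the case for the moderate diet conditional on a glucose benefit "without elevated risk of hypoglycemia or ketoacidosis are shown". Section 1 includes the risk of ketoacidosis in the aim.

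**The concern.** A settled-state window suits the efficacy question. For a safety endpoint it removes the days when insulin and carbohydrate are most likely to be out of step. The protocol recognises this: section 2.5 has staff review insulin at the start of each phase because the diet is changing, and section 1 says that doses are hard to predict and standardise. Section 3 puts the planned reduction at 40% of carbohydrate energy (600 against 1,000 kcal, and 1 - 600/1000 = 0.40).

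If lows became more frequent for a week or two after one of the diets was started and then subsided, the CGM safety endpoint would show no difference. The condition on hypoglycaemia risk could then be judged met from data that exclude the period of greatest interest. The data that would settle the matter are already being collected.

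**Working it through.** **Plan's own figure.** The only computed figure in the article is the sample size of 52, which concerns mean glucose. A two-sided paired t-test with difference 1 mmol/l, alpha 0.05 and 2.5 mmol/l taken as the SD of the paired differences gives n = 52 (power 0.808). It reproduces on that reading, and the present point does not depend on it.

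**Coverage of the CGM safety endpoint.** Inputs: diet period 28 days (section 2.1); window 14 days (Table 3, footnote 1).
- Covered: 14/28 = 50% per diet.
- Omitted: days 1-14. All four scheduled calls (days 1, 4, 7, 14, counted from the start of the diet) fall there.

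**What the window can hide.** Let d1 be the between-diet difference in time below 3.9 mmol/l in days 1-14, and d2 the difference in days 15-28. With equal CGM coverage, the planned endpoint estimates d2 and the full period estimates (d1 + d2)/2. The documents give no time-below-range figures, so the values below are purely illustrative, with d2 = 0:

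| d1 (points) | Planned endpoint | Full 28 days | Days 1-14 |
|---|---|---|---|
| 1 | 0 | 0.5 | 1 |
| 2 | 0 | 1 | 2 |
| 4 | 0 | 2 | 4 |

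The last row corresponds to 8% then 4% on one diet against 4% throughout on the other. The full-period figure halves a transient effect, so days 1-14 need to be shown separately as well.

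**Can severe hypoglycaemia fill the gap?** It is the only hypoglycaemia endpoint not tied to the last 2 weeks. Inputs: 54 randomized (section 2.2), 28 days per diet, everyone assumed to complete both diets.
- Exposure per diet: 54 x 28 / 365.25 = 4.14 person-years.
- The article gives no event rate. Over an assumed 0.05 to 0.5 per person-year, expected events per diet are 0.05 x 4.14 = 0.2 to 0.5 x 4.14 = 2.1.
- In the first fortnight alone, half of that: 0.1 to 1.0.

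Counts of this size are unlikely to reveal a transient excess.

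**Ketoacidosis (secondary).** With zero events on a diet:
- One-sided 95% upper limit for the rate: -ln(0.05)/4.14 = 0.72 per person-year.
- As a proportion of subjects per 4-week period: 1 - 0.05^(1/54) = 5.4%.

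A zero count is therefore compatible with a rate that nobody would call reassuring.

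**The case against.** The strongest reply has four parts.

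*The early fortnight is not unobserved.* A reader might infer that it is missing from the safety assessment altogether. The article does not support that. Only one of the four safety endpoints carries the footnote. Ketones are measured twice a week during both diets (section 2.7), and adverse events are recorded at every visit and call (section 2.8), including the calls in the first fortnight. This stands, and it confines the point to CGM-measured lows.

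*The window has a reason.* In the last 14 days patients dose on their own, so lows reflect diet rather than staff-guided adjustment. Using the same window for mean glucose lets benefit and harm be read together. This also stands. The window is not an error as a steady-state summary, and nothing shows that it was applied to safety by oversight. It does not follow that it should be the only window for a safety endpoint.

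*The statistical analysis plan may add a full-period analysis.* It may, and section 2.8 leaves room for one. The endpoint as published nevertheless fixes the narrower window.

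*Ketoacidosis.* A reader might infer that the protocol already claims no elevated ketoacidosis risk, or that its Poisson mixed model is a defect because it has no finite rate ratio when one diet has no events. Neither reading is supported. The sentence in the Abstract and section 3 is conditional, and a fallback for sparse events is ordinary analysis-plan content. What remains is a caution on interpretation.

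**Conclusion.** The point holds for CGM-measured hypoglycaemia. Table 3 excludes half of each diet period, 14 of 28 days, from time below 3.0 and below 3.9 mmol/l. The excluded half contains the diet change and the supported insulin adjustment. This sits badly with the Abstract and with the strength claimed in section 3, and section 2.8 is silent on the window.

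The exclusion is established from the text alone. Whether a transient excess exists, and how large it is, cannot be known from the article, so the time-below-range figures above are illustrations. The statement that severe events cannot stand in for the missing CGM data rests on the assumed 0.05 to 0.5 events per person-year and on full completion by 54 subjects; dropout would lower the expected counts.

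The ketoacidosis arithmetic supports care in wording only and does not carry the point. The change is worth making before database lock. It affects neither the primary analysis nor the sample size.

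**What to change.** 1. Keep the last-14-day window for the efficacy endpoints and as the steady-state summary of time below range.
2. Add a prespecified safety analysis of time below 3.0 and below 3.9 mmol/l over the whole 4-week period and over days 1-14 separately, by diet, with confidence intervals for the difference.
3. Base any statement on elevated risk of hypoglycaemia on both the early and the late window.
4. Bring the Abstract, section 2.8 and section 3 into line with Table 3, so that each states which CGM window it refers to.
5. For ketoacidosis, report event counts per diet with exact upper confidence limits, and do not read zero events as evidence of no elevated risk.

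Cost: no new data, visits or subjects are needed. There will be more CGM gaps to handle in the longer window. Because enrolment is complete and the endpoints are published, the addition must be documented and dated as a supplement to the safety analyses, fixed before database lock. Adding it, rather than redefining the published endpoint, avoids an endpoint change.

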The primary efficacy analysis will be the analysis of the mean difference in mean glucose levels measured by CGM during the last 2 weeks of the treatment period between moderate carbohydrate diet and traditional diabetes diet on the Full Analysis Set. The treatment effect will be estimated using linear mixed effects models for normally distributed variables as described above.

All statistical tests will be two-sided and conducted at the 5% significance level. To account for multiple testing, a sequential testing procedure will be employed. If a test gives a significant result at the 0.05 significance level, the total probability mass of 0.05 will be transferred to the next endpoint in the test sequence until a nonsignificant result is achieved. All these significant tests will be considered confirmatory. *p*-values and confidence intervals of remaining endpoints will be presented descriptively.

Statistical analyses will be performed using SAS statistical software version 9.4. A Statistical Analysis Plan with a detailed description of all planned analyses will be completed and signed before the database is locked. Once all study data are collected and entered, the database will be reviewed for completeness, accuracy, and consistency. At a formal Clean File meeting the database will be declared locked, and the analysis can start.

The target sample size was set to 52 subjects to detect a clinically relevant difference in mean glucose levels of 1 mmol/l between treatments, assuming a within subjects’ standard deviation of 2.5 mmol/l, paired *T*-test, 80% power, significance level *α* = 0.05. The standard deviation was estimated on data from the GOLD cross-over trial (34).

## Discussion

3.

This is a description of the protocol for a randomized controlled cross-over study investigating the impact of a moderate carbohydrate diet compared to a traditional diabetes diet with higher carbohydrate content on glycemic control and other health parameters in T1D.

Diet with moderate carbohydrate content (30 percent of total energy from carbohydrates) is considered safe in healthy populations and for people with type 2 diabetes but is quite different compared to the traditional diabetes diet (50 percent of total energy from carbohydrates) as generally recommended regarding amount of fat and carbohydrates (5, 6). A diet high in saturated fat and low in fiber, fruits and complex carbohydrates is not considered healthy (5, 6). Therefore, it was important to make both intervention diets healthy in terms of other nutrients not only macronutrients, which is why both diets included vegetables, root vegetables, nuts and seeds, fish and shellfish, legumes and unsaturated fats like olive or rapeseed oil as well as a focus on carbohydrate quality in both diets such as choosing wholegrains and foods rich in fiber with low glycemic index (7–13). Trying to make both intervention diets healthy and safe we choose a moderate amount of carbohydrates instead of a low- or very low carbohydrate diet. This was also because the diet should be tolerable and easy to incorporate into everyday life as well as making it easier to comply with for longer time periods, not only for the study period. Further, although it may seem like the difference in carbohydrate content is relatively small, the intervention group will get 40% less carbohydrates (e.g., 600 kcal instead of 1,000 kcal for a person with a daily energy intake of 2,000 kcal) which we consider to be a clinically relevant difference. Moreover, considering that participants may not fully comply to the diets we will also make the per protocol analyses including only the subjects that fully complied to the protocol and the diets.

The randomized design reduces the risk of confounding factors associated with various diets that can be related to blood glucose control and often difficult to account for in observational studies. Further, by using a cross-over design all participants were given the opportunity to try both diets and serve as their own controls eliminating interpatient variability. Because insulin therapy is different between all subjects, we made a structured management plan regarding changes in insulin regimen during the study to keep it as comparable as possible between the two diet periods. Use of CGM to measure blood glucose levels on all subjects continuously throughout the study provides detailed data about fluctuations in glucose control during changes in diet. Dietary interventions and all study material were developed by a registered dietitian and considered healthy and safe according to available evidence. Limitations include possible carry-over effects due to the cross-over design making interpretation of results potentially more difficult. Blinding of study participants was not possible because knowledge of carbohydrate content was crucial for patients. Existing knowledge, or preference, of low carbohydrate diets may lead to bias in favor of moderate carbohydrate diet versus traditional diabetes diet. It is difficult to measure diet compliance accurately as it is based on participant experience and self-reporting. Over- or underreporting of diet is common when it comes to food records or dietary assessments (35, 36).

The study period of 12 weeks and active intervention periods of each 4 weeks was planned to be relatively short since we wanted participants to comply to changes in diets and advanced study related procedures including food diaries, ketone levels and masked CGM. The main goal of the trial is to evaluate if different carbohydrate content in diet influences glucose levels. Moreover, the use of masked CGM-data for key endpoints capturing differences in glucose patterns continuously gives an opportunity to capture the current glucose effects during each treatment period. Hence, the current study will show if a lower content of carbohydrates in diet *per se* leads to more stable glucose levels and if ketone levels are influenced. However, it is important to notice that if the intervention diet leads to improved glucose control it will be essential to evaluate whether such a diet can be kept over long time periods with sustained effects on glucose control.

In summary, this study seeks to increase knowledge about the effects of dietary carbohydrate intake on glycemic control and other health parameters in patients with T1D. If beneficial effects on mean blood glucose level without elevated risk of hypoglycemia or ketoacidosis are shown, a moderate carbohydrate diet may be a treatment option for people with T1D that have unsatisfactory blood glucose levels. If shown to have no beneficial effects, this study will hopefully increase knowledge among healthcare professionals whether moderately decreasing carbohydrate intake is safe when educating patients about diet.

## Ethics statement

The studies involving human participants were reviewed and approved by the regional ethics committee of Gothenburg, Sweden (No. 473-17). The patients/participants provided their written informed consent to participate in this study.

## Abbreviations

AE: adverse event
BMI: body mass index
CGM: continuous glucose monitoring
CONSORT: consolidated standards of reporting trials
DTSQ: diabetes treatment satisfaction questionnaire
HbA1c: glycated hemoglobin
isCGM: intermittent scanned continuous glucose monitoring.
SAE: serious adverse event
SD: standard deviation
SPIRIT: standard protocol items: recommendations for intervention trials.
T1D: type 1 diabetes mellitus.
